### Plans to promote participant retention and complete follow-up {18b}

Mentor involvement with young fathers and female partners is a critical aspect of participant retention; active mentors lead to engaged participants. Thus, to prevent mentor drop-out, the implementing partners publicly acknowledge the mentors’ efforts and involvement at the parish and sub-county level both in-person and in-community media. This leads to an elevated status of the mentors and has been instrumental in maintaining mentors’ sustained engagement and motivation. In addition, the program also keeps mentors and young couples engaged via post-session reflection meetings and in community recognition opportunities on special occasions and in community media. While no direct financial remuneration is provided to either the mentors or young couples, the program ensures that mentors and families are aware of local existing resources and social and economic government initiatives. These include the following: Healthcare services such as access to maternal and child health, reproductive health, HIV/AIDS prevention, and treatment; Education services such as early childhood development, universal primary, secondary and vocational education services; Government initiatives which help families improve their economic stability through financial support and entrepreneurship such as Village Savings and Loan Association (VSLA), Parish Development Model (PDM), Youth Livelihood Program (YLP), Uganda Women Entrepreneurship Program (UWEP), and Graduating to Resilience (GROW); Digital inclusion initiatives, including internet access centers and AI-driven advisory services that promote greater access to information and digital literacy; and linkages registration for national identification cards.

### Data management {19}

Quantitative data from the male and female questionnaires will be collected electronically by trained RAs on tablets programmed using the Kobo ToolBox platform and transferred to the secure Kobo ToolBox cloud account. Back-up data will also be stored on secure servers. Access to the identifiable data is restricted to the Co-I and trial statistician and requires password access. The Co-I and trial statistician are responsible for ensuring the quality of the data, as well as cleaning and anonymizing the survey data before sharing with the PI via encrypted electronic files for further analyses. The PI will not have access to identifiable data. All anonymized data for analysis will be saved in a password-protected server at the University of California San Diego. In addition to these steps, the study will use a number of other data handling and quality control approaches:*Standard Operating Procedures Booklet.* The research team will develop a standard operating procedures (SoP) booklet for RAs (enumerators) and Field Supervisors (FS). The SoP booklet will detail survey enumeration instructions and best practices on how to handle challenging scenarios in the field, and provide detailed instructions on how to administer questions that may be difficult for participants to follow, such as those that use a Likert scale.*Questionnaire and Enumeration Training and Piloting.* RAs and FS will pilot the item phrasing and data collection platforms during their training to ensure they understand the context and meaning of the items and are familiar with the tablet data collection platform. The SoP booklet will be updated with key insights gained during the RA/FS training and pre-testing of data collection tools.*Skip Logic and Validation*: The survey will be programmed with skip logic and validation to ensure valid responses are captured and each question is answered. RAs will also be required to take the GPS reading to validate the respondents’ interview location. This GPS data will be used to verify if RAs are truly at the designated location when collecting data, providing a layer of accountability and reducing the chance of fraudulent reporting. Wireless internet will be activated on all devices and data transmitted in real time to undertake routine and ongoing quality control checks during the data collection period.*Field Supervision and Spot Checks*. Each of the six data collection teams will have an FS. Following the overall RA/FS training, the field supervisors will receive additional field supervision training on data quality control and troubleshooting of field-related challenges. The team lead and each FS will also carry out random checks on a range of forms captured by different RAs to ensure completeness of questionnaires. Each FS will also undertake troubleshooting for challenging cases and scenarios in the field. Any issues identified that need retraining will be immediately dealt with. A field supervision meeting with all RAs in the same geographical localities will be undertaken daily, and once a week a general field supervision meeting will be conducted with all sub-teams.*Data Quality Control Sample.* We will use a quality control sample of approximately 1% (37 respondents) distributed across the six data collection teams, with approximately 6 respondents per team at each round of data collection. This sub-sample will be re-interviewed on some key questions by a different group of RAs for quality control purposes. If the index of inconsistency is > 20, data collection will be paused until additional data quality control measures can be implemented such as re-training, re-interviewing the respondents, contacting the RAs for explanations, and changing the RAs if necessary.*Unique Participant Identifiers*. The database will capture an individual respondent’s unique identifier (ID). The survey is also programmed to generate an automatic ID for all respondents which will reject any duplicate records during data upload. The IDs will include assigned unique variables for district, sub-county, parish, age, and sex, using a coding scheme known only to the co-I, each FS, team leads, and study statistician. Only the co-I and the study statistician will have the final key linking the respondent ID to the name of the individual respondent.

### Confidentiality {27}

All data will be kept confidential and stored on a secure server. Data access will be restricted to those conducting data analysis on the study team, and each will have access to the data only through password protected log-in. Anonymization of data will be carried out by the co-I and study statistician to maintain participant confidentiality. Names of participants will not appear on any of the data collection forms. The statistical modelling required to answer the project’s questions will require only the participants’ identification number and not their names. Upon generation of the data, it will be coded so that the personal identity and individual data from the study participants are traceable only with the code key which will be held by the study researchers; no one else will have access to it. The code key required to transform anonymized data into identifiable data will be stored within the encrypted drives, within encrypted, password protected cloud folders. No identifiable participant information will be reported in publications. Analyses will use pooled data and will be restricted to regional estimates as the smallest unit of analysis. Once analysis is complete, the link and folders will be deleted, and all data collection materials will be handed over for custody or destruction.

### Plans for collection, laboratory evaluation and storage of biological specimens for genetic or molecular analysis in this trial/future use {33}

No genetic or molecular analysis of biological material is planned in this trial.

## Statistical methods

### Statistical methods for primary and secondary outcomes {20a}

The primary analysis will follow an intention-to-treat (ITT) approach, where all study participants will be analyzed according to their original randomization assignment at baseline. To evaluate intervention effects on primary and secondary outcomes, we will employ difference-in-differences (DID) regression models, which are well-suited for analyzing longitudinal data. DID estimation estimates the causal effect of the intervention by comparing changes in outcomes over time between the treatment and control groups while controlling for unobserved time-invariant characteristics, provided the parallel trends assumption and the Stable Unit Treatment Value Assumption (SUTVA) hold. To account for the complex survey design, we will incorporate random effects in the DID regression models to address clustering at the sub-county level (the unit of randomization). Additionally, clustered standard errors will be used to correct for within-individual autocorrelation and intra-cluster correlation (ICC) at the village level. Where necessary, sample survey weights will be applied to adjust for any imbalances in sub-county or district-level characteristics. As noted above in the “Sample size” section on sample size, we apply Bonferroni correction to account for multiple comparisons in primary outcomes while maintaining an overall 5% level of statistical significance for the trial.

Since all trial outcomes are binary, we will use mixed-effects logistic regression models for the primary endline analysis. As a supplementary analysis, we will estimate causal effects in terms of risk differences using mixed-effects linear models, implemented via the *xtdidregress* and *xtreg* commands in Stata. Individual-level observations will be analyzed rather than cluster-averaged data, following methodologies outlined by Hussey & Hughes (2007) and Baio et al. (2015)) [54, 55]. Let $${Y}_{ijk}$$ denote an outcome of individual *i* from *j*th subcounty and *k*th region measured at time period *t*, and modelled as:$$logit(P({Y}_{ijkt}=1)={\beta }_{j}+\lambda {G}_{i}+\alpha {T}_{i}+\gamma {(GT)}_{i}$$where $${\beta }_{j}$$ is the random effects term for the sub-counties (with $${\beta }_{j} \sim N\left(0,{\tau }_{\beta }^{2}\right)$$.); $$\lambda$$ is fixed effect of randomization group (G_*i*_ = 1, if exposed to intervention; and G_*i*_ = 0, otherwise); $$\alpha$$ is a fixed effect of time (T_i_ = 0 if baseline, T_i_ = 1 if endline), and $$\gamma$$ is an interaction effect of time and group. Predicted margins will be used to compute the average causal effect or equivalently the ITT estimand.

For follow-up analysis, we will implement a three-time-point panel model to assess the persistence of treatment effects nine months post-intervention closure. Additionally, a two-time-point analysis (comparing endline and follow-up) will be conducted as a sensitivity analysis to evaluate short-termeffects.

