## Interventions

### Explanation for the choice of comparators {6b}

Random allocation is made between intervention and wait-list control groups, as randomized at the sub-county level. The intervention group will receive the REAL Fathers intervention within a month after the screening process, while the wait-list control group will receive the REAL Fathers intervention after follow-up data collection (wave three) is conducted. Participants in the control group will continue to access standard care and services that are already available in their communities. These include the following: village health team visits and referrals to clinics when applicable; early childhood development centers and programming; family planning and social-economic interventions from Government, as described in further detail in the “Plans to promote participant retention and complete follow-up” section below.

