### Sample size {14}

Sample size is based on calculations using the outcome measure of proportion of young fathers who apply positive parenting behaviors. Based on the pilot studies on REAL Fathers intervention in Uganda, and to ensure sufficient statistical power of sub-group analyses at the regional level to obtain the largest sample size necessary, we assume only 40% of the young fathers use positive parenting skills at baseline [40]. From pilot studies, the REAL Fathers intervention should improve this proportion by at least 10% (effect size on absolute scale) by the endline [40]. The sample size computation is based on the formula:$$n=\frac{[2*{\left({Z}_{\alpha /4}+{Z}_{1-\beta }\right)}^{2}*\overline{P }(1-\overline{P })]}{{({P}_{1}-{P}_{0})}^{2}}\times Deff$$where:

*n* = minimum sample size of individuals required per arm of study

*Z*_α/4_ = the critical value of the standard normal variate at significance level of α/4 (*α* is assumed to be 0.05 or 95% certainty for improvement in the four primary outcome indicators). By setting the critical *Z* value corresponding to an alpha level of 0.0125 (i.e., α/4), our sample size calculation adjusts for multiple outcome testing while maintaining an overall 5% level of statistical significance for the trial.

*Z*_1-β_ = the critical value of the standard normal distribution at a power of 1-β (assumed to be 0.80 or 80% power)

*P*_0_ = the value of positive parenting indicator at the baseline; assumed 40%

*P*_1_ = the value of positive parenting indicator at the endline; assumed to be 50%—a 10-percentage point increase based on pilot studies$$\overline{P } = \frac{{P}_{1}+{P}_{0}}{2}$$

*Deff* = clustering effect, assumed to be 2.3

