### Recruitment {15}

A combination of listing and stratified simple random sampling approaches will be applied while selecting study participants. The participants will be recruited within the 24 districts (four districts in each region). In each district, a three-stage sampling design will be applied. In the first stage, two sub-counties will be selected at random considering the urban/rural divide (see Table 7). From the selected sub-counties, up to four parishes will be selected at random. From each selected parish, up to 12 villages will be selected at random and a census/listing of all eligible young fathers as per the inclusion criteria (Table 2, above) will be listed with the help of individuals familiar with the villages (i.e., members of village health teams (VHTs) and village leaders (local council chairpersons or LC1 executives) to generate a sampling frame. A total of 24 villages will be sampled from 4 randomly selected parishes in two randomly selected sub-counties in each district.

**Table 7 Tab7:** REAL Fathers external evaluation selected sample

	**District**	**Sub-county**	**Randomization**
1	Amuria	Akeriau	Intervention
2	Amuria	Morungatuny	Control
3	Bugiri	Bulidha	Intervention
4	Bugiri	Iwemba	Control
5	Buikwe	Nkokonjeru Tc	Intervention
6	Buikwe	Buikwe Tc	Control
7	Dokolo	Okwalongwen	Intervention
8	Dokolo	Agwata	Control
9	Hoima	Kyabigambire	Intervention
10	Hoima	Kigorobya	Control
11	Ibanda	Keihangara	Intervention
12	Ibanda	Ishongororo	Control
13	Iganga	Nawanyingi	Intervention
14	Iganga	Nakalama	Control
15	Isingiro	Kabuyanda	Intervention
16	Isingiro	Kashumba	Control
17	Kamuli	Bulopa	Intervention
18	Kamuli	Kagumba	Control
19	Katakwi	Katakwi	Intervention
20	Katakwi	Toroma	Control
21	Kayunga	Kangulumira	Intervention
22	Kayunga	Kayunga	Control
23	Kikuube	Bugambe	Intervention
24	Kikuube	Kiziranfumbi	Control
25	Kiryandongo	Bweyale Tc	Intervention
26	Kiryandongo	Kiryandongo Tc	Control
27	Kole	Ayer	Intervention
28	Kole	Bala	Control
29	Lira	Aromo	Intervention
30	Lira	Ogur	Control
31	Luwero	Bamunanika	Intervention
32	Luwero	Katikamu	Control
33	Masindi	Miirya	Intervention
34	Masindi	Pakanyi	Control
35	Mayuge	Imanyiro	Intervention
36	Mayuge	Mpungwe	Control
37	Mbarara	Kagongi	Intervention
38	Mbarara	Kashare	Control
39	Nakasongola	Nabisweera	Intervention
40	Nakasongola	Wabinyonyi	Control
41	Oyam	Ngai	Intervention
42	Oyam	Otwal	Control
43	Rubirizi	Katerera	Intervention
44	Rubirizi	Kirugu	Control
45	Serere	Kateta	Intervention
46	Serere	Kyere	Control

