## Assignment of interventions: allocation

### Sequence generation {16a}

The study will be implemented in 24 districts in six geographical regions of Uganda. As noted above, in each district, a simple random sample of two sub-counties will be taken. These sub-counties will be randomly allocated to either the treatment or control condition (1:1 within each district) using the Mersenne Twister algorithm via the RAND function in Microsoft Excel [52]. For subsequent follow-up studies (midline and endline), all enrolled participants will be re-interviewed at midline and endline surveys. (See Table 7 for sample randomization of sub-counties data).

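### Village-level clustered standard errors and a time-constant sub-county intercept leave the group-by-time test unprotected if the randomised sub-counties change differently over time

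*Protocol article*

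**What the plan says.** The unit of allocation is clear. Explanation for the choice of comparators {6b} describes the groups "as randomized at the sub-county level". Sequence generation {16a} says "These sub-counties will be randomly allocated to either the treatment or control condition (1:1 within each district"). With two sub-counties in each of 24 districts, that makes 24 per arm.

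Statistical methods {20a} divides the handling of correlation between two devices:

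- For the sub-county: "we will incorporate random effects in the DID regression models to address clustering at the sub-county level (the unit of randomization").
- For the lower levels: "clustered standard errors will be used to correct for within-individual autocorrelation and intra-cluster correlation (ICC) at the village level".

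The model equation in the same section has one intercept per sub-county, which "is the random effects term for the sub-counties" and has no time index. It adds fixed effects of group and time, and a coefficient that "is an interaction effect of time and group". That coefficient carries the treatment effect. The equation has no sub-county-by-period term.

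The per-outcome threshold comes from Sample size {14}, which uses a critical value "corresponding to an alpha level of 0.0125 (i.e., α/4"). Statistical methods {20a} repeats the Bonferroni correction and the overall 5% level.

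**The concern.** The treatment effect is a difference between arms in change over time. In a balanced linear model, a sub-county effect that is equal at baseline and endline drops out of that difference exactly. In the logistic model it does so approximately. What remains at sub-county level is differential change: a local programme, a poor harvest or a shift in norms that moves one sub-county and not its neighbour. The primary model has no term for this.

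Village-level standard errors do not supply one. They treat villages as independent, although villages in the same sub-county share both the allocation and any local change. Shared change is then averaged over many villages when it should be averaged over 24 sub-counties per arm.

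At stake is the error rate of the primary tests. If sub-counties drift apart, an ineffective programme has more than a 1.25% chance per outcome of being declared effective. The DiD regressions planned under Interim analyses {21b} would be affected in the same way.

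**Working it through.** **Inputs from the document**

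- Per-outcome level: 0.05 / 4 = 0.0125, as stated. Sidedness is not stated. I take it as two-sided, so the critical value is z = 2.498.
- Size: 1872 dyads per arm / 24 sub-counties = 78 each. With 10% attrition, 78 × 0.9 ≈ 70 followed.
- Village ICC: 0.20, the lower end of the pilot range 0.20–0.24 in Sample size {14}.
- Villages per sub-county, V: the document allows two readings. Recruitment {15} says "A total of 24 villages will be sampled from 4 randomly selected parishes in two randomly selected sub-counties in each district", so 24 / 2 = 12. Sample size {14} takes the 78 couples per arm in a district from 6 villages, so V = 6.

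**Assumptions, not in the document**

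- Sub-county ICC ρ = 0.01, 0.02 or 0.05, counted within the village ICC of 0.20.
- Cluster autocorrelation c = 0.8 or 0.5, the same at sub-county and village level.
- Individual correlation over time 0.4.
- One shared shock per sub-county and period.

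**Formulas** (linear change scores, unit total variance, per sub-county)

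- Sub-county change: A = 2ρ(1 − c)
- Village change: B = 2(0.20 − ρ)(1 − c) / V
- Individual change: D = 2 × 0.8 × (1 − 0.4) / 70 = 0.01371
- True variance: T = A + B + D
- Variance that village clustering estimates: W = A / V + B + D
- True type I error: 2 × [1 − Φ(2.498 × √(W / T))]

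**One case in full** (V = 12, ρ = 0.02, c = 0.8)

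A = 2 × 0.02 × 0.2 = 0.00800. B = 2 × 0.18 × 0.2 / 12 = 0.00600. T = 0.02771 and W = 0.00067 + 0.00600 + 0.01371 = 0.02038. W / T = 0.735, its square root is 0.858, and the error rate is 3.2%.

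**True type I error against nominal 1.25%**

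| V | c | ρ = 0 | ρ = 0.01 | ρ = 0.02 | ρ = 0.05 |
|---|---|---|---|---|---|
| 12 | 0.8 | 1.25% | 2.2% | 3.2% | 7.0% |
| 12 | 0.5 | 1.25% | 2.9% | 4.9% | 11.5% |
| 6 | 0.8 | 1.25% | 1.8% | 2.5% | 5.0% |
| 6 | 0.5 | 1.25% | 2.1% | 3.2% | 6.9% |

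**Three-cohort case.** Suppose every sub-county contributes to all three cohorts, shocks are independent between cohorts, and each village belongs to one cohort. Then A in T becomes A / 3 and W is unchanged. With 12 villages the rates for ρ = 0.01, 0.02 and 0.05 are 1.5%, 1.7% and 2.5% (c = 0.8), and 1.6%, 2.1% and 3.6% (c = 0.5). With 6 villages they are 1.4%, 1.5% and 1.8%, and 1.4%, 1.6% and 2.1%.

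**Simulation check.** Null trials with binary outcomes were generated from a logit model: 3,000 per setting, 48 sub-counties, about 70 followed in each, and 6 or 12 villages. They were tested by DiD on the risk-difference scale.

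| SD of sub-county-by-period effect (logit) | Village-clustered SE |
|---|---|
| 0 | 1.1–1.4% |
| 0.10 | 1.7–2.1% |
| 0.15 | 2.2–2.7% |
| 0.20 | 3.1–3.7% |
| 0.30 | 5.5–8.1% |

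Clustering at the sub-county with t on 46 df gave 0.97–1.50% in every setting. Model-based standard errors from the random-intercept model alone gave 0.4–1.2% with no drift and about 5–7% at SD 0.30, so the intercept is no safeguard either.

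**The case against.** The strongest reply is that the harm rests on inputs the document does not give. That stands. No sub-county ICC, autocorrelation or drift is stated, and at zero drift village clustering holds its level. A reader might infer that the confidence intervals for all primary outcomes are too narrow, or that a fixed multiple of 1.25% applies. The document supports neither. The inflation depends on drift, on which village count is right, and on how cohorts map to sub-counties. The three-cohort case is a favourable bound, but the document does not rule it out, and Criteria for discontinuing or modifying allocated interventions {11b} says cohort effects will be accounted for in the DiD analyses.

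Second, the quoted sentence names the correlations to be corrected and does not expressly fix the variance cluster. That is fair. Village is still the natural reading, because the sub-county is assigned to the random effect. If the sentence meant something else, the random-intercept model alone still fails under larger drift.

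Third, a reader might infer that no small-sample degrees of freedom will be used. The article is silent, and an analysis plan may settle it, so that silence is no finding.

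Fourth, neither the formula nor the simulation fits the planned mixed logistic model. This limits the precision of the figures. It does not affect the reason the intercept drops out.

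The hierarchical models under Methods for additional analyses {20b} do look at sub-county heterogeneity. They are additional analyses and leave the primary test unchanged.

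**Conclusion.** The point holds as a stated rule that does not match the design: the sub-county is randomised, but nothing in the primary specification captures sub-county-specific change. If such change occurs, the variance of the group-by-time effect is understated and the 0.0125 level is not secured.

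Under the assumptions listed, the true error is about 2.2–11.5% with 12 villages per sub-county, 1.8–6.9% with 6, and 1.4–3.6% if shocks average over three cohorts. It is 1.25% with no drift. Confidence is high in the structure and moderate in the size, since the figures are linear approximations resting on an assumed drift.

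**What to change.** Rewrite the two sentences on clustering in Statistical methods {20a} so that inference for both the logistic and the risk-difference DiD models rests on the randomised unit, by one of two routes:

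- sub-county-clustered standard errors with a t reference suited to 48 clusters in 24 district pairs (46 df, or 23 if the pairing is used); or
- a sub-county-by-period random effect alongside village and individual effects, with degrees of freedom to match.

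Do not use village-level clustered standard errors as the basis for inference. Apply the same rule to the interim and follow-up models.

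The change is to wording and code and needs no extra data. If drift is present, intervals widen by √(T / W). In the worked case this is √(0.02771 / 0.02038) = 1.17, or about 17%. If drift is absent, the t reference alone widens them by about 4% (2.60 / 2.50, 46 df) to 8% (2.71 / 2.50, 23 df).

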Based on the Uganda Bureau of Statistics 2019 population projections and Uganda Demographic and Health Survey 2016 data, only 4% of the male population (16–25 years) are young fathers who are married or cohabiting [6]. According to the latest Uganda population and housing census, the average village size is about 100 households [49]. Thus, no more than 10 young men (16–25 years) will be fathers whose eldest child is below the age of three years. To be on the conservative side, we assume that, on average, only 8 young fathers are eligible for the study from any given village. Let $$\overline{m }$$ denote this average and suppose *cv* is the coefficient of variation in the number of fathers across the different villages, and ρ is intra-cluster correlation (ICC). Pilot studies on the REAL Fathers intervention approximated ICC of 0.20–0.24 at the village level. Thus:$$Deff=\left(1+\left(\left({cv}^{2}+1\right)\overline{m }-1\right)\rho \right)=\left(1+\left(\left(0.063+1\right)\times 7-1\right)\right)\times 0.20=2.3$$

Based on the above parameters and an attrition rate of 10% between the baseline and endline, a total of 1872 couple dyads is required per study arm (3744 in total). This translates to 156 couples per district: 78 in each study arm from 6 villages; and 312 couples per geographical region. This makes an assumption of treatment effect size of 10% on indicators at project level and 80% statistical power and 95% certainty (alpha = 0.05).

The study is being conducted across regions characterized by diverse subcultures, both between and within locations. To ensure sufficient power to detect potential heterogeneity in treatment effects across key subcultural groups, we adjusted the sample size accordingly. Drawing on pilot data, we anticipate a moderate level of effect heterogeneity across these subcultures. According to Ford and Norrie (2016) [50] and Kent et al. (2018) [51], moderate heterogeneity corresponds to a coefficient of variation (CV) of approximately 20% in treatment effects. To account for this, we increased the originally planned sample size by 20%, resulting in a target of 2200 participants per study arm.

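### Conditional use of survey weights in the primary ITT analysis leaves its target population open; fix the rule in advance (minor)

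*Protocol article*

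**What the plan says.** The section on statistical methods for primary and secondary outcomes {20a} sets out the primary ITT analysis. After random effects for sub-counties and clustered standard errors, it adds: "Where necessary, sample survey weights will be applied to adjust for any imbalances in sub-county or district-level characteristics". It then prints a mixed-effects logistic model with a random sub-county effect and fixed effects for arm, time and their interaction. That model contains no weights and no district term. The effect is summarised thus: "Predicted margins will be used to compute the average causal effect or equivalently the ITT estimand".

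On the design, Sequence generation {16a} says that "in each district, a simple random sample of two sub-counties will be taken" and that allocation is "1:1 within each district". Table 7 agrees: each of the 24 districts has one intervention and one control sub-county. Sample size {14} fixes the numbers: "This translates to 156 couples per district: 78 in each study arm from 6 villages". Recruitment {15} adds further random stages: "From the selected sub-counties, up to four parishes will be selected at random", then villages, then fathers from a village listing.

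Sample size {14} also expects moderate variation in the treatment effect across subcultures and defines it: "moderate heterogeneity corresponds to a coefficient of variation (CV) of approximately 20% in treatment effects".

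**The concern.** The sentence ties a tool to a purpose and makes its use conditional. Both parts need attention.

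- **Purpose.** Sampling weights undo unequal selection probabilities. Chance imbalance between randomised arms is normally handled by the randomisation strata and by prespecified baseline covariates. Weighting to the sampling frame is not designed to remove it.
- **Condition.** The weighted and unweighted effects refer to different populations: the eligible fathers in the sampled areas, or the enrolled sample with its equal number per district. When effects vary, which the protocol expects, the two differ. A rule that weights the primary analysis only if needed leaves open which effect is primary.

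At stake are the meaning of the primary effect and some precision. The design effect of 2.3 covers clustering and variation in village size, with no component for unequal weights.

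**Working it through.** **1. What weights can and cannot correct here.** Two sub-counties are drawn in each district, and 78 couples are taken in each whatever the number of eligible fathers. Selection probabilities therefore differ between districts and sub-counties. That is a proper reason for sampling weights, but the sentence does not give it. Between arms, the district mix is equal by design: one sub-county per arm in each district, with 78 couples targeted in each. It can differ only if recruitment falls short or attrition is unequal. Sub-county characteristics can differ between arms by chance, but selection-probability weights do not aim at that difference.

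**2. The plan's own figures.**
- Per arm: 78 × 24 districts = 1,872, as stated; both arms 3,744, as stated.
- Design effect: 1 + ((0.063 + 1) × 7 − 1) × 0.20 = 2.29, stated as 2.3.
- The printed sample-size formula with the listed inputs does not give 1,872. With two-sided 0.0125 it gives 2 × (2.498 + 0.842)² × 0.45 × 0.55 / 0.10² × 2.3 ≈ 1,270, and 1,270 / 0.9 ≈ 1,411. With one-sided 0.0125 it gives about 1,202. This is a separate matter. It matters here only because it explains why unweighted power at 1,872 exceeds the planned 80%.

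**3. Power under weighting.** Inputs from Sample size {14}: 40% against 50%, attrition 10%, design effect 2.3, alpha 0.0125. Two-sided testing is my assumption, because the article does not state sidedness. The CV of the weights is also an assumption and is shown as a range, because the article gives no weights.

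Effective n per arm = N × 0.9 / 2.3 / (1 + CV²)

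Power = Φ(0.10 / √(0.495 / effective n) − 2.498), where 0.495 = 2 × 0.45 × 0.55

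| CV of weights | 1 + CV² | Effective n, N = 1,872 | Power, N = 1,872 | Effective n, N = 2,200 | Power, N = 2,200 |
|---|---|---|---|---|---|
| 0 (unweighted) | 1.00 | 733 | 91% | 861 | 95% |
| 0.3 | 1.09 | 672 | 88% | 790 | 93% |
| 0.5 | 1.25 | 586 | 83% | 689 | 89% |
| 0.7 | 1.49 | 492 | 74% | 578 | 82% |

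N = 2,200 is shown because Sample size {14} ends with that target, while the same section, Trial design {8} and Recruitment {15} give 1,872.

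The factor 1 + CV² is the usual approximation when weights are unrelated to the outcome. Multiplying it by the clustering design effect is a further approximation.

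**4. Difference between the two effects.** The weighted minus the unweighted average effect equals r × CV of weights × SD of the effects, where r is the correlation between weight and effect. With a 10-point effect and the protocol's 20% variation, the SD is 2 points. The largest possible difference (r = 1) is 0.6 points at CV 0.3, 1.0 at 0.5 and 1.4 at 0.7. A weaker correlation gives less.

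**The case against.** The best defence is that the sentence never says the imbalance is between arms. It closes a run of remarks about accounting for the complex survey design, and the Discussion calls the cohort representative. Read that way, the imbalance is of the sample against the population, and survey weights are the right tool. The mention of district-level characteristics fits this reading better, since arms are matched on district. This stands: a reader might infer that the protocol misuses sampling weights, but the text does not establish it. It does not rescue the conditional wording, because weighting for representativeness changes the target population and should then be a fixed decision.

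Three other strong readings also go beyond the document.
- **District characteristics can never differ between arms.** The 78 per arm is a target, the numbers of parishes and villages are upper limits, and 10% attrition is expected. The realised district mix could differ somewhat.
- **The analyst may choose the more favourable result.** The article does not say when, or by whom, the need for weights is judged. Imbalance and selection probabilities can both be assessed without outcome data.
- **The trial loses its planned power.** Only the assumed CV of 0.7 with 1,872 per arm falls below 80%.

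Finally, the definition of the weights may stand in an analysis plan that is not shown; the article says one will be registered and published before data analysis. Its absence here is not the point. The point is the conditional rule that the article does state for the primary analysis.

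**Conclusion.** The concern holds as a minor point. The rule as written makes weighting of the primary ITT analysis conditional and gives a purpose that selection-probability weights do not serve if balance between arms is meant. If representativeness is meant, the tool is sound, but the primary effect refers to one population or another depending on a trigger that is not fixed. Either way the sentence needs rewriting.

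The size is modest. Power moves from about 91% to between 88% and 74% over weight CVs of 0.3 to 0.7 at 1,872 per arm, and stays at about 82% or more at 2,200. The two effects could differ by at most about 0.6 to 1.4 points on a 10-point effect. These figures rest on assumed weight CVs, two-sided testing, the protocol's design effect and its positive-parenting proportions, which concern a secondary outcome. They do not show that the planned result would be wrong.

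**What to change.** Replace the conditional sentence with a fixed rule:

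- The primary ITT model is unweighted.
- It includes district, the randomisation stratum, as a fixed effect.
- Sub-county imbalance is handled through a short list of baseline covariates named in advance.
- Weights are defined as inverse selection probabilities and used only for descriptive regional estimates or one labelled sensitivity analysis of the primary effect.

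The cost is wording. District is already known for every participant, so its term needs no new data; with 24 districts it adds 23 parameters to the model. The downside is that the primary effect then refers to the enrolled sample with equal numbers per district. The effect for the wider eligible population is reported as the sensitivity analysis.
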